### Timelines

The study application for funding was approved by the National Health and Medical Research Council (NHMRC) in May 2016, and funding commenced in January 2017. A pilot study to inform the main trial was undertaken from May to December 2017. Recruitment and training of the PARTNER CST occurred between May and October 2017. Recruitment for the RCT commenced in March 2018 and is due for completion in February 2019. The trial is due for completion in March 2020 after the 12 months data collection is complete.

### Adverse events

The risks for participants involved in this study are minimal. There will be multiple mechanisms for identifying serious adverse events (SAEs) that occur during the trial. Firstly, if the CST become aware of any SAE, they will inform the patient’s GP for follow-up and will advise the Chief Investigator and Trial Coordinator as soon as possible. Secondly, if a patient cannot be contacted over a four week period or at the end of the trial, the trial staff will contact the GP to confirm if the participant is still alive or has had any serious medical issues that have restricted their participation. Finally, the follow-up surveys and the health diary will ask patients to self-report any adverse events they may have experienced during the course of the trial. All SAEs will be reported to the approving HREC’s.

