### Intervention

The PARTNER model includes management by both the GP and the new CST service to improve patient outcomes (Fig. 2). The implementation intervention aims to facilitate the GPs’ role in the PARTNER model. Patient participants will all have an initial visit to their GP for confirmation of an OA diagnosis and a knee OA focused consultation as their GP sees fit. Patient participants of GPs allocated to the intervention group will receive care described in the PARTNER model. Delivery of the PARTNER model depends on GPs receiving the implementation intervention (GP intervention) and the patient receiving care for 12 months by the CST service. These two components are described below. GPs in the control group will receive no intervention and their patients will not have access to the CST. After the initial GP consultation, control patient participants will continue to receive ‘usual GP care’ for their knee OA.

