Phase 1 – first 18 weeks. The patient will be contacted once per fortnight on average, or as agreed with the patient. The CST will provide ongoing self-management advice and support, to address the goals and activities of their tailored care plan.

2.Phase 2–6 month maintenance period (or until the end of the 12-month intervention period). Patients will be encouraged and supported to develop strategies to self-manage their OA. They will be contacted monthly, or as agreed, to monitor their progress and address any new or ongoing issues as required. Patients can still be re-referred to their GP or other allied health professionals if an escalation of care is required. However, patients cannot elect to participate in the HWFL weight-loss program during this phase.

The CST will provide updates to the GPs on the progress of their referred patients via cdmNET at three time points (after initial consultation, after 18 weeks and at the end of the patient’s involvement with the CST), or on request by the GP. The reports will detail any strategies and actions agreed with the patient, and their progress to date. The CST will refer the patient back to their GP if they require a medication review, or if they have any other medical condition that affects participation in the trial or an escalation of care. If the situation is urgent the CST member will ring the GP to discuss. If the situation is routine the CST will correspond with the GP via cdmNET.

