#### Statistical analysis

GP practices and individual participants will be analysed according to their randomised group, using intention-to-treat. Those practices that fail to recruit any patients or withdraw from the study prior to collecting data from any patients will be excluded from the analysis [68]. Descriptive statistics at the participant and GP practice level will be presented to allow comparison of treatment groups at baseline. Analyses will be conducted at the participant level. For continuous outcome measures, differences in mean change (baseline minus follow-up) will be compared between groups using generalised estimating equations (GEEs) to account for within-practice correlation with exchangeable correlation, robust standard errors, and adjusting for the baseline value of the outcome variable and stratification variables. For binary outcomes, GEEs will be fitted using a logit link function assuming an exchangeable correlation structure and robust variance estimation, adjusting for stratification variables, with results presented as odds ratios. To aid interpretation, risk differences will also be calculated using marginal probabilities [69]. Multiple imputation will be applied to missing participant-level data from GP practices which do not withdraw from the study before data collection and that recruit at least one patient [70].

An independent Data Safety and Monitoring Board (DSMB) will meet periodically to monitor the quality of trial data and the safety of patients. The DSMB may recommend continuing the trial or modifying the trial, or stopping the trial early. A recommendation to stop the trial may only be made to protect the safety of trial participants if there is clear evidence of a clinically important harmful effect.

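### One of the three routes for identifying serious adverse events exists only in the intervention arm, so all-source counts by arm could be biased towards apparent harm

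*Protocol article*

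**What the plan says.** The Adverse events section of the protocol article describes three routes by which SAEs are identified.

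- **CST awareness.** "Firstly, if the CST become aware of any SAE, they will inform" the GP, and they also alert the Chief Investigator and the Trial Coordinator promptly.
- **GP check.** Trial staff ask the GP about any patient who has been out of reach for four weeks or at the end of the trial. No restriction by arm is stated.
- **Self-report.** In addition, "the follow-up surveys and the health diary will ask patients to self-report any adverse events". Again no restriction by arm is stated.

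The first route cannot operate in the control arm. The Intervention section says: "GPs in the control group will receive no intervention and their patients will not have access to the CST".

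CST contact is frequent. For the first 18 weeks, "The patient will be contacted once per fortnight on average, or as agreed with the patient". In the six-month maintenance phase, "They will be contacted monthly, or as agreed, to monitor their progress".

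The only stated use of safety data across patients is the DSMB's remit (Statistical analysis). It may recommend stopping only "if there is clear evidence of a clinically important harmful effect". The article sets out no by-arm tabulation or test of SAEs, and does not say that the source of an SAE is recorded.

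**The concern.** Arms can be compared on SAEs only if events have a similar chance of being found in each. Here intervention patients speak regularly to health professionals who must pass on any SAE they learn of, and control patients have no counterpart. An event that a patient never reports in a survey or diary can still be recorded in the intervention arm, through the CST, but is likely to be lost in the control arm.

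Timing differs too. An SAE known to the CST is passed on at once, while a control event may wait for the next survey. Even if final capture were equal, an interim DSMB table could hold more of the intervention arm's events.

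Two things are at stake: the evidence on which the DSMB judges harm, and the safety comparison in the final report. A true excess could also be dismissed as better detection, and a true benefit could be cancelled by it. An analysis plan cannot repair this later unless the source of each event was recorded at collection.

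**Working it through.** The article gives no SAE rate, expected count or capture share, so there is no stated figure to reproduce. The check has three steps.

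**1. Planned CST contacts per intervention patient** (The PARTNER care support team)

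- Phase 1: 18 weeks ÷ 2 = 9
- Phase 2: 6 months × 1 = 6
- Total: about 15 as a planned average, against none for controls

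**2. What both arms share**

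- Surveys go to all patients monthly (health service use) and at 3, 6 and 12 months (Trial procedures).
- Table 2 lists an adverse event questionnaire at 0, 6 and 12 months.
- The health diary also records hospitalisation (Outcome measures, healthcare expenditure item).
- The GP check applies to patients who cannot be reached.

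For events spread evenly in time, the mean wait until the next enquiry is 6 ÷ 2 = 3 months if only the Table 2 questionnaire elicits them. It is 1 ÷ 2 = 0.5 month if a monthly diary does; the monthly frequency of the diary is an assumption.

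**3. Effect on counts under equal true risk**

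From the article: 572 patients at 1:1, so 572 ÷ 2 = 286 per arm.

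Assumed: true SAE risk *p* in both arms; share *s* of SAEs captured by the common routes; share *c* of the remainder that the CST adds, in the intervention arm only.

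Recorded ratio (intervention ÷ control) = [*s* + (1 − *s*)*c*] ÷ *s*

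| *s* | *c* = 0 | *c* = 0.25 | *c* = 0.5 | *c* = 0.8 |
|---|---|---|---|---|
| 1.0 | 1.00 | 1.00 | 1.00 | 1.00 |
| 0.9 | 1.00 | 1.03 | 1.06 | 1.09 |
| 0.7 | 1.00 | 1.11 | 1.21 | 1.34 |
| 0.5 | 1.00 | 1.25 | 1.50 | 1.80 |

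Worked case, *p* = 0.10, *s* = 0.7, *c* = 0.5:

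- Control: 286 × 0.10 × 0.70 = 20.0 patients with a recorded SAE (proportion 0.070)
- Intervention: 286 × 0.10 × 0.85 = 24.3 (proportion 0.085)
- Ratio: 0.085 ÷ 0.070 = 1.21

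Chance of a nominally significant intervention excess (two-sided 5%, clustering ignored):

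- SE under no difference = √(2 × 0.0775 × 0.9225 ÷ 286) = 0.02236
- SE under the recorded proportions = √[(0.070 × 0.930 + 0.085 × 0.915) ÷ 286] = 0.02235
- Φ[(0.015 − 1.96 × 0.02236) ÷ 0.02235] = Φ(−1.29) ≈ 0.10

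Over *p* = 5% to 15%, *s* = 0.5 to 0.9 and *c* = 0.25 to 0.8, that chance runs from 3% to 65%. It passes 50% only at *p* = 15%, *s* = 0.5, *c* = 0.8.

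In a comparison limited to the common routes, the expected ratio is 1.00 and the chance 2.5%, provided those routes are equally complete in the two arms.

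**The case against.** The strongest reply is that the article plans no comparison of pooled SAE counts. It says how SAEs are found and reported; tabulation may sit in a full protocol, analysis plan or DSMB charter not shown here. That is correct, and the point is not about a missing analysis. It concerns ascertainment, which the article does fix, and fixes differently by arm.

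Second, the CST route is passive. No SAE question at CST contacts is described, contacts are by agreement, the first comes about a month after enrolment, and patients in the 18-week weight-loss programme may have fewer CST contacts in that period. Fifteen contacts are therefore not fifteen SAE enquiries. This stands and limits the size.

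Third, shared collection is substantial: monthly surveys, further surveys at 3, 6 and 12 months, the diary and the GP check. Only events that the CST learns of and the common routes never capture distort the final counts. This also stands, and the distortion could be nil.

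Fourth, the DSMB exercises judgement under a demanding criterion and does not act on raw counts. True, but it can allow for unequal detection only if it sees where events came from.

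Fifth, restricting the comparison to patient self-report would be unsafe, since it would lose deaths and incapacitating events that the GP check finds and would take known SAEs away from the DSMB. This stands; the all-source table has to remain.

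A reader might go further and infer that the trial will show spurious harm, or that SAEs are detected through the CST alone. The documents support neither: two of the three routes are open to both arms, and nothing in the article gives the share of events they miss.

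**Conclusion.** The point holds as a design asymmetry of unknown size. One of three SAE routes, resting on about 15 planned contacts on average, exists in the intervention arm only, and no equivalent contact with controls is described. If true risk is equal and the common routes work equally well in both arms, all-source counts are either unbiased or biased towards apparent harm; a real benefit could likewise be masked.

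The recorded ratio is 1.0 if the common routes miss nothing or the CST adds nothing, and about 1.1 to 1.3 if they capture 70% and the CST finds a quarter to four fifths of the rest. Larger ratios need the common routes to miss about half of all SAEs. The risk, the capture share and the CST share are all assumptions; the article supplies none of them. That is enough to ask for a change in data collection, but not enough to predict a false safety signal.

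**What to change.** - Record the source and the date of detection of every SAE. If several routes find the same event, record each.
- Keep the all-source SAE table for the DSMB, and leave individual reporting as it is.
- Beside it, add a between-arm comparison limited to the routes common to both arms: surveys, health diary and the GP check for patients who cannot be reached. Always include deaths, however they became known.
- Count an event found by both the CST and a common route in the common-route table. List CST-only events separately.

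The cost is a small addition to the SAE form and one extra table. The common-route table omits CST-only events, which remain visible in the all-source table. It could also err towards apparent safety if patients who have told the CST about an event do not repeat it in a survey, so the two tables need to be read together. It further assumes that the GP check is triggered in the same way in both arms, which should be confirmed.

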#### Future use of data

Information collected for this study may be used in future projects or submitted to a public database so that other researchers can access it and use it. At this stage, it is not known what these other projects will involve. We will seek ethical approval before using the information in these future projects, and any identifying information will be removed. All participants (general practices, GPs and patients), will be advised of the potential for future use of their de-identified data in the Patient Information Statement and Consent Forms.

## Discussion

Given knee OA is one of the most prevalent and disabling chronic diseases, even small reductions in ineffective practices with small improvements in care may lead to marked cost savings and reductions in the individual and societal burden of the disease. If the PARTNER intervention rationale is correct and implementation is successful, the results will have major significance for Australia with potential implications internationally, including potential relevance to low- and middle-income settings in the context of remotely-delivered care. The intervention is intentionally complex and targets both GPs and patients. By improving the capacity of GPs to offer their patients support for behavioural change through the CST, we hope to ensure uptake and maintenance of exercise and weight loss and better satisfaction with the care they are provided. We also hope to improve access to high-quality self-management support and behavioural counselling for patients, and by so doing improve adherence to effective conservative non-drug treatment including exercise and weight loss, thus reducing the OA burden.

We have clear intentions for subsequent implementation by planning to ensure the intervention is acceptable, feasible, aligned with current Australian models of care and to assess its cost-effectiveness. We will assess the barriers and facilitators to more widespread implementation and work closely with stakeholders including consumers, government and insurers to ensure policy recommendations stem from this work if found to be effective and cost-effective.

## Abbreviations

ABS: Australian Bureau of Statistics
ADL: Activities of Daily Living
AQoL-8D: Assessment of Quality of Life Instrument
ASES: Arthritis Self-Efficacy Scale
BFMS: Brief Fear of Movement Scale
B-IPQ: Brief Illness Perception Questionnaire
BMI: Body Mass Index
CBT: Cognitive Behavioural Therapy
cdmNet: Chronic Disease Management Network software
CSQ: Pain Coping Strategies Questionnaire
CST: PARTNER Care Support Team
DHS: Commonwealth of Australia Department of Human Services
DSMB: Data Safety Monitoring Board
EC-17: Effective Consumer Scale
GPs: General Medical Practitioners
HREC: Human Research Ethics Committee
HWFL: Osteoarthritis Healthy Weight For Life Program
KOOS: Knee injury and Osteoarthritis Outcome Score
MBS: Medical Benefits Scheme
Medicare: Universal health care system funded by the Commonwealth Government of Australia
NHMRC: Australian National Health and Medical Research Council
NICE: National Institute for Health and Clinical Excellence
OA: Osteoarthritis
OA-QI: Osteoarthritis Quality Indicator Questionnaire
OARSI: Osteoarthritis Research Society International
PAM: Patient Activation Measure
PARTNER: Optimising primary care management of knee osteoarthritis trial
PASE: Physical Activity Scale for the Elderly
PBS: Pharmaceuticals Benefits Scheme
PCS: Pain Catastrophising Scale
PHQ-9: Patient Health Questionnaire
PHReNet: New South Wales Primary Health Care Research Network
PROMIS™: Patient-Reported Outcomes Measurement Information System
QALYs: Quality-adjusted Life Years
QI&CPD: Quality Improvement and Continuing Professional Development
QoL: Quality of Life
RACGP: Royal Australian College of General Practitioners
RCT: Randomised Controlled Trial
REDCap: Research Electronic Data Capture software
SAE: Serious Adverse Event
UNSW Australia: University of New South Wales, Sydney, Australia
VicReN: Victorian Primary Care Practice-Based Research Network
WPAI:OA: Work Productivity and Activity Impairment Questionnaire: Osteoarthritis of the Knee
